## Abstract

**Introduction:**

Community health workers (CHWs) are critical to healthcare delivery in low-resource settings but often lack formal clinical training, limiting their decision-making. Large language models (LLMs) could provide real-time, context-specific support to improve referrals and management plans. This study aims to evaluate the potential utility of LLMs in assisting CHW decision-making in Rwanda.

**Methods and analysis:**

This is a prospective, observational study conducted in Nyabihu and Musanze districts, Rwanda. Audio recordings of CHW-patient consultations will be transcribed and analysed by an LLM to generate referral decisions, differential diagnoses and management plans. These outputs, alongside CHW decisions, will be evaluated against a clinical expert panel’s consensus. The primary outcome is the appropriateness of referral decisions. Secondary outcomes include diagnostic accuracy, management plan quality, and patient and user perceptions to ambient recording of consultations. Sample size is set at 800 consultations (400 per district), powered to detect a 15–20 percentage point improvement in referral appropriateness.

**Ethics and dissemination:**

Ethical approval has been obtained from the Rwandan National Ethics Committee (RNEC) (Ref number: RNEC 853/2025) in June 2025, recruitment started in July 2025 and results are expected in late 2025. Results will be disseminated via stakeholder meetings, academic conferences and peer-reviewed publication.

**Trial registration number:**

PACTR202504601308784.

STRENGTHS AND LIMITATIONS OF THIS STUDYFirst prospective evaluation of a large language model-assisted decision support system for community health workers in a real-world, low-resource setting.Directly supports Rwanda’s ongoing digital Community Health Worker Application platform rollout.The blinded expert panel provides robust reference standards for comparison.Study limited to two districts in Rwanda; findings may not be generalisable to other settings.Observational design precludes assessing clinical impact on patient outcomes, requiring evaluation in interventional trials.

## Introduction

 Community health workers (CHWs) play a critical role in delivering primary healthcare services in low-resourced and middle-resourced countries, particularly where access to trained medical professionals is often limited.^1^ CHWs act as the first point of contact for communities, providing essential services including triaging, diagnosing and providing basic treatment for a limited number of common health conditions, with a particular focus on maternal, child and infectious disease care.^2 3^

In Rwanda, CHWs typically have limited formal clinical training,^4^ relying on targeted training programmes and following a structured national decision-making algorithm for managing common health conditions.^5 6^ This algorithm has recently been embedded within the newly introduced Community Health Worker Application (CHWApp), a smartphone-based digital decision-support tool, designed to standardise care and guide referrals. The CHWApp rollout forms part of Rwanda’s digital health transformation strategy and, as of December 2024, has been deployed to 1500 CHWs nationwide. However, while digitisation has enhanced record-keeping and streamlined some processes, the clinical decision-making protocols underpinning the CHWApp have remained unchanged. It continues to use a limited, closed-ended decision tree, which may inadequately capture atypical presentations or conditions beyond its predefined scope, potentially negatively affecting patient outcomes and healthcare system efficiency.

Large language models (LLMs) are advanced artificial intelligence (AI) systems trained on extensive text datasets,^3^ enabling them to process and generate human-like text outputs. In healthcare, LLMs have shown potential for improving clinical decision support, diagnostic reasoning and care optimisation.^7 8^ Most published evaluations of LLM performance, however, have taken place in high-income healthcare settings, and little is known about their utility in frontline, low-resource environments, particularly for non-professional healthcare providers like CHWs.^9^

Integrating LLMs into CHW workflows offers the opportunity to provide real-time, context-specific, evidence-based guidance that could improve the appropriateness of referrals and reduce delays in recognising serious conditions. A recent benchmarking exercise evaluating multiple LLMs for alignment with expert medical consensus on questions posed by CHWs demonstrated promising accuracy rates, particularly for newer generation models.^10^ Nonetheless, there remains a critical need for prospective, real-world studies evaluating how LLMs perform when applied to actual patient encounters in low-resource settings.

This study aims to address this evidence gap by prospectively evaluating the appropriateness of referral decisions made by CHWs and an LLM, using a clinical expert panel as the reference standard, in two districts of Rwanda. The findings will inform the feasibility, safety and potential value of integrating LLM-based clinical decision support tools into community healthcare workflows in LMIC settings.

## Methods and analysis

### Study design

This study is a prospective, multisite, observational study designed to evaluate the clinical decision-making performance of CHWs and an LLM in the management of new patient complaints in Rwanda. The study uses real-world patient consultations conducted by CHWs in community settings, with no alteration to existing clinical workflows or patient care pathways. During the study period, CHWs will audio record their routine consultations with eligible patients using a dedicated study application installed on their smartphones. These recordings will be securely uploaded to a central data server and subsequently transcribed. These recordings will be translated from Kinyarwanda to English using an AI-based translation tool. The resulting English transcripts will be anonymised and then provided as input to the LLM, alongside a structured clinical prompt (see online supplemental material 1). The LLM will generate a differential diagnosis list, a referral decision and a proposed management plan for each case. To evaluate the appropriateness of both the CHW decisions (standard of care) and the LLM decisions, a panel of independent general practitioners (GPs), each with a minimum of 2 years of clinical experience in Rwanda, will review each patient consultation transcript using a prespecified, study-specific evaluation rubric.

### Study setting

The study will be conducted in two districts of Rwanda: Nyabihu and Musanze, located in the country’s north-west region. These districts were purposely selected to capture variability in CHW digital tool use and to reflect a range of geographic, socioeconomic and healthcare delivery environments. Nyabihu district represents a largely rural population with over 900 CHWs already using the national smartphone-based CHWApp decision-support platform as part of Rwanda’s digital health transformation strategy. In contrast, Musanze district includes a mix of rural and semiurban communities, and while smartphones have been distributed to 150 CHWs in the area, the CHWApp had not yet been implemented at the time of study commencement. CHWs in Musanze, therefore, continue to use traditional paper-based consultation and referral tools. This diversity in CHW workflow and decision-support mechanisms provides a relevant and representative context to assess the comparative value of LLM decision-support in settings with varying levels of digital health integration.

### Eligibility criteria and recruitment

Eligible CHWs will be identified by UGHE in collaboration with the Rwanda Biomedical Centre (RBC) and district health offices. A Microsoft Excel RAND function will be used to randomly sample 50 CHWs from a list of eligible CHWs in each district. Recruitment will be facilitated via telephone contact by study research assistants (RAs), followed by an in-person consent process conducted at local health centres. The inclusion criteria for CHWs are as follows:

Completion of RBC national CHW training curriculum.At least 3 months of active clinical practice experience.Ability to communicate in either Kinyarwanda or English.

The exclusion criteria for CHWs are as follows:

CHWs out of active service for more than 1 month.Intention to relocate or travel outside the study district during the study period.Declining or unable to provide informed consent.

CHWs that consent to participate will undergo study-specific training covering the protocol, their role in the study, standard operating procedures, principles of informed consent and trial runs of the study procedures prior to study commencement (see online supplemental material 1).

All patients whose consultations are provided by participating CHWs during the study period will be considered for inclusion. Patient eligibility will be assessed by CHWs, and prior to each consultation, CHWs will provide eligible patients with an explanation of the study and seek written informed consent. CHWs will follow a standardised consent procedure using forms written in Kinyarwanda. Only consenting patients will be enrolled, with no impact on care for those declining participation (see online supplemental material 1). Patient participants attending with the first presentation of any health-related complaint are eligible, including paediatric patients (<18 years of age); those aged 12–18 years will be asked to assent in addition to seeking their guardian’s consent.

Patient participants will be excluded from the study if they are receiving CHW visits for reasons other than new health-related complaints, such as weight checks, vaccinations or routine antenatal care. Patients requiring immediate or emergency medical care, including trauma cases and medical emergencies, will also be excluded. Additionally, non-verbally communicative participants, those in consultation environments that do not allow for audio recording, and patients who do not speak Kinyarwanda or English will not be eligible. Finally, patients who are unable or unwilling to be contacted for follow-up outcomes or to attend a health centre if referred will be excluded from participation.

### Consultation and related events

On consent, the CHW will initiate audio recording of the entire clinical consultation using the StudyApp. CHWs will be instructed to conduct consultations according to their usual practice, guided either by the national CHW decision-making algorithm (on paper or via CHWApp). The consultation recording—and all subsequent LLM outputs—will not be used to influence the care of the patient. The CHW will be asked to provide their usual standard of care, and there are no restrictions placed on that care as a result of this study. Following the consultation, CHWs will administer a brief structured patient experience questionnaire to assess perceptions of being recorded (see online supplemental material 1).

### Follow-up and related events

As part of standard CHW practice, patients will be followed up on day 5 to assess symptom progression and treatment outcomes. In addition, the study protocol includes a day 14 follow-up for research purposes. CHWs will complete a structured follow-up form (see online supplemental material 1) on the StudyApp, capturing information on symptom resolution (resolved, unchanged, worsened, deceased), any further health service use and counter-referral details for referred patients.

Patients reporting full symptom resolution at the day 5 follow-up will not undergo the day 14 follow-up. CHWs will also photograph and upload any counter-referral forms (providing feedback to the CHW for continued care in the community) received from health centres for referred patients (see online supplemental material 1).

After the data collection period, RAs will conduct short user experience surveys and four focus group discussions of 8–12 CHWs to get insight into their experience of being recorded and any challenges faced (see online supplemental material 1).

Patient participant flow is summarised in figure 1.

**Figure 1 F1:**
[figure not shown]
Study participant flow. CHW, community health worker.

### LLM output generation

The recording and transcript will be automatically uploaded and accessed on a secure data warehouse. The first 10–20 transcript samples will be considered a pilot and excluded from the primary analysis. Instead, they will be used to assess recording quality and transcription accuracy, perform exploratory analysis and prompt engineering of the LLM (GPT-4). This process will involve examining the initial transcripts to optimise the LLM’s performance in generating useful outputs and refining how the prompts are structured to elicit the most accurate and relevant responses. By testing and adjusting the prompt structures based on these transcripts, we will effectively ‘tune’ the LLM to improve its clinical decision-making capabilities.

Following this, the research team will omit the interaction’s outcomes (ie, the CHW’s management and referral decision) and feed the transcript and prompts to the LLM to: (1) produce a referral decision, (2) suggest five differential diagnoses in order of likelihood and (3) propose a management plan

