### Expert evaluation of CHW outputs and LLM outputs

12 independent GPs, each with a minimum of 2 years of clinical experience in Rwanda and valid Rwanda Medical and Dental Council licences, will be recruited for this study. They will be organised into four panels of three to evaluate each patient–CHW consultation transcript using a study-specific evaluation rubric (see online supplemental material 1). This evaluation will provide a ground truth against which the LLM and CHW outputs will be measured. Evaluators will receive training to standardise the evaluation approach. This training will include an overview of the study protocol and detailed instructions on using the evaluation rubric. During the training, 10 simulated cases will be reviewed to establish a common frame of reference across the panel and to familiarise evaluators with the rubric.

Everyone in the triplet group of evaluators will independently review the case transcript, make a diagnosis and develop a management plan. The evaluator’s tasks for each objective are as follows:

Based only on the day 0 consultation transcript, a reference standard should be determined to decide on the appropriateness of the CHW and LLM referral decisions.Review the day 0 consultation transcript and the 5-day or 14-day follow-up information to establish a reference standard for evaluating the correctness of the CHW and LLM referral decisions.Assess the diagnostic accuracy of the LLM through:

 Establishing one ‘most likely’ diagnosis based on all the information provided. Independently scoring the appropriateness of the differential diagnosis list according to a prespecified rubric. Assessing whether the diagnosis provided in the counter-referral (or, if unavailable, the panel’s ‘most likely’ diagnosis) is the top-ranked or is included within the top five differential diagnoses suggested by the LLM.

4. Assess the appropriateness of the LLM-generated management plan according to the evaluation rubric.

After the initial assessments, the average response for the Likert scale question will be calculated. The panel will also review and discuss the open-ended responses, such as the ‘most likely’ diagnosis, and collaboratively reach a consensus on the diagnosis.

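### The removal rule for the LLM's input covers only the CHW's management and referral decision, so a voiced CHW diagnosis or algorithm classification is not excluded

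*Protocol article*

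**What the plan says.** All references are to the protocol article.

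- **Removal rule (LLM output generation).** After the pilot transcripts, the team leaves out the outcomes of the interaction, spelt out in a parenthesis, and passes on the rest: "CHW’s management and referral decision) and feed the transcript and prompts to the LLM". The parenthesis opens with *ie*, so it defines the omitted outcomes as two items.
- **What is recorded (Consultation and related events).** After consent, "the CHW will initiate audio recording of the entire clinical consultation using the StudyApp". Usual practice is "guided either by the national CHW decision-making algorithm (on paper or via CHWApp").
- **What CHWs do (Introduction).** Their work is described as "providing essential services including triaging, diagnosing and providing basic treatment for a limited number of common health conditions". The same section calls the CHWApp's logic a closed-ended decision tree.
- **LLM input (Study design).** Here the input is described without any removal step: "The resulting English transcripts will be anonymised and then provided as input to the LLM".
- **Diagnostic scoring (Expert evaluation).** Assessors check whether the counter-referral diagnosis, or failing that the panel's own, "is the top-ranked or is included within the top five differential diagnoses suggested by the LLM".
- **Primary outcome.** The CHW's actual referral decision and the LLM's are each compared with a blinded GP panel's decision, which rests on the day 0 transcript alone.

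**The concern.** The investigators already accept that the LLM should not see what the CHW decided. The question is whether the stated cut is wide enough. A CHW who names a disease, or reads out the category that the algorithm returned, has stated neither a management step nor a referral. An editor who follows the rule exactly would leave those words in.

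Two results depend on this. The first is the LLM's diagnostic accuracy. The model is asked for five ranked diagnoses from text that may contain one the CHW has already offered. The article has no CHW diagnostic accuracy to set beside the LLM's, so a reader could not tell the model's own reasoning from repetition. The second is the primary contrast, which sets the LLM's accuracy against the CHW's performance alone. That reads naturally only if the two decisions are reached separately. Under a decision tree, a classification may point to the referral even after the referral sentence is deleted.

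**Working it through.** No figure in the plan is in dispute, so there is none to reproduce. The check is a reading of the text, followed by an illustration of size.

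**Step 1. What the rule covers**

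| Content of the recording | Named for removal? |
|---|---|
| Referral decision | Yes |
| Management | Yes |
| CHW's stated diagnosis | No |
| Classification from the paper or app algorithm | No |
| History, questions, signs, test results | No (rightly kept) |

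No other section fills the third and fourth rows; Study design mentions only anonymisation. Under Data quality assurance, a case is discarded if its recording lacks the history or the referral outcome. Every analysed recording therefore includes the point at which the CHW states a conclusion, and every transcript needs this edit.

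**Step 2. What the text does not show**

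No section says that CHWs voice a diagnosis or read classifications aloud, or how often. Leakage is therefore possible under the rule, but not documented.

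**Step 3. Effect on the primary contrast**

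Editing the LLM's input leaves the CHW's accuracy unchanged. Let *g* be the share of consultations in which leaked text turns a wrong LLM referral decision into a right one, and *l* the share in which it does the reverse. The LLM-minus-CHW difference then moves by *g* − *l*. The article gives neither, so the sign is unknown.

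Inputs for the illustration, from Sample size: CHW accuracy 73.3%, GPT-4o accuracy 91.2%, gap 91.2 − 73.3 = 17.9 points.

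*Case A: the LLM simply follows the CHW in a share k of consultations (an assumption).*

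LLM accuracy = (1 − k) × 91.2 + k × 73.3, so gap = 17.9 × (1 − k).

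| k | Gap (points) |
|---|---|
| 0 | 17.9 |
| 0.10 | 16.1 |
| 0.20 | 14.3 |
| 0.34 | 11.8 |
| 0.50 | 9.0 |

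The gap falls below the 15-point target once k exceeds 1 − 15/17.9 = 0.16. It falls below the stated detectable difference of 11.8 points once k exceeds 1 − 11.8/17.9 = 0.34.

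*Case B: the LLM gains from correct CHW impressions and is not misled by wrong ones (g > 0, l = 0).* The gap widens. The ceiling on the gain is 100 − 91.2 = 8.8 points, which would take the gap to 100 − 73.3 = 26.7.

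**Step 4. Effect on top-1 and top-5 accuracy**

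The upward error is the share of scored cases in which the voiced diagnosis is correct, the LLM would have missed it unaided, and the LLM adopts it. A wrong voiced diagnosis that displaces a correct one works the other way. The article gives no inputs for either, so no figure is offered.

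**The case against.** The strongest reply is that the comparator itself is protected. The CHW's referral decision is one of the two items removed. The LLM is scored against the GP panel, or against the counter-referral or panel diagnosis, and never against the CHW's diagnosis. This stands. A reader might infer that the LLM can copy the very comparator it is measured against, but the article does not support that. At most a precursor reaches the model, from which the referral might be inferred.

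It can also be said that this is a condensed article with supplementary material, that line-by-line editing rules belong there, and that staff may read outcomes more widely than the parenthesis does. This stands in part. It is why the claim is that such statements are not excluded, rather than that they remain. But the article does state a rule and closes its list, and a rule that relies on each editor's wider reading needs tightening.

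The size in Case A is fairly attacked. The share k is assumed. The formula gives the followed cases average accuracy for both deciders. The 73.3% is a GP benchmark figure standing in for CHWs, and 91.2% belongs to GPT-4o while the article names GPT-4 as the model. Copying a weaker decider would also shrink the LLM's advantage rather than create one. All of this stands, and Case B shows that shrinkage is not the only possibility.

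A reader might further infer that leakage differs between paper and CHWApp consultations and so distorts that comparison. Nothing in the article shows that conclusions are voiced more often with either tool, so this is speculation.

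Finally, broad deletion could harm the LLM unfairly. It cannot see the patient, and a spoken danger sign may be the only evidence of that sign. This stands and limits the fix. An unredacted input might also be defended because the eventual use is decision support within CHW workflows. However, the plan has already chosen to remove the CHW's decision, and the LLM's diagnostic accuracy is reported as its own.

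**Conclusion.** The concern holds in a limited form. As written, the rule removes the CHW's management and referral decision and does not exclude a voiced diagnosis or an algorithm classification. Where one is voiced, top-1 and top-5 accuracy may be credited with the CHW's diagnosis, and the LLM's referral decision may not be independent of the CHW's. The diagnostic results are the more exposed, because nothing that corresponds to a diagnosis is on the removal list.

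The frequency is not documented and the direction for the primary contrast is unknown. The figures in the working show only that moderate copying would matter against the plan's own targets. They rest on an assumed share and on planning values, and do not estimate a bias that has occurred.

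**What to change.** In LLM output generation, extend the removal to the CHW's stated diagnosis and any classification output of the paper or app algorithm. State that history, the CHW's questions, observed signs (including danger signs reported as findings) and test results are kept. Amend Study design so that both sections describe the same edited input.

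Flag each transcript in which such a statement was voiced, and each in which it could not be cleanly removed. Report the counts, and repeat the primary and top-1/top-5 analyses without the flagged transcripts. Apply the seven-recording minimum per CHW before they are set aside, so that the sensitivity analysis does not also drop CHWs.

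The cost is some extra editing time and judgement on transcripts that are already being edited. Transcripts already processed would need an offline LLM re-run, which affects no patient because LLM outputs are not used in care. The change needs ethics committee and sponsor approval, as Ethical considerations requires. The LLM may then work from slightly less text than the panel reads; this should be reported as a limitation.
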